### Recruitment {15}

The clinic typically sees 200 patients per year for ST with 65% of the patients being nonsmokers, leaving a total of 130 patients who are eligible to participate in the study. Of those 130 individuals, 10% of people will have severe cases of periodontal disease that will require antibiotics with ST. This equates to 117 patients per year that remain eligible to participate in the study. We are estimating that 60% of people will agree to participate on the study, given the time commitment to the intervention. Previous data we collected showed 64.7% of patients undergoing periodontal surgery reported using one or more dietary supplements [29]. We anticipate that the same proportion of patients undergoing ST will be highly motivated to further support their recovery and will agree to the study. Therefore, the recruitment for 48 participants in the pilot study will be completed within 1 year. It is expected that participants from the pilot study will be included as part of the full trial sample size.

## Assignment of interventions: allocation

### Sequence generation {16a}

A computer-generated list of random numbers will be used to create a sequential set of unique codes with an equal number of participants assigned to each of the two groups.

### Concealment mechanism {16b}

A member of the research team will be responsible for the randomization and labeling of the packages. Each intervention package will contain 100 sachets of either the control or intervention product. The packages will be labeled with the unique codes that were generated. There will be a master list, kept in a locked office at the clinic, which matches the unique code with the corresponding treatment.

### Implementation {16c}

The inulin or placebo will be prepared ahead of time and stored at the clinic. The packaging will ensure that the specific treatment cannot be visually ascertained. The participants will be randomized to receive a package at the clinic and the unique code on the package will become the code that identifies the participant. Participants will be instructed to use this code to complete their dietary assessments at home. This code will also be used to label saliva samples. At this time, participants will receive verbal instructions on how to take the supplement and ask any questions they might have. Written instructions will also be included in the package to refer to when they are back home.

## Assignment of interventions: Blinding

### Who will be blinded {17a}

The trial participants and care providers will be blinded to the group allocation.

### Procedure for unblinding if needed {17b}

In the case of emergency and a participants’ allocated intervention needs to be revealed, a staff member at the clinic will match the master list to the list that identifies the participants’ name and code.

## Data collection and management

### Plans for assessment and collection of outcomes {18a}

Clinical data, including periodontal outcomes and anthropometric measurements, will be collected from electronic patient files and recorded in a specialized spreadsheet. This will be combined with data from the online dietary assessments and saliva analyses.

### Plans to promote participant retention and complete follow-up {18b}

Participants regularly attend the appointments where we will be collecting data for their clinical care. Thus, we have designed the intervention around this schedule. As previously mentioned, side effects will be minimized by taking the intervention as two separate doses during the day. Also, we have minimized the burden on the participants by having the treatments individually packaged.

### Data management {19}

Dietary questionnaires will be filled out online and will be downloaded from the ASA24 website onto a spreadsheet file that will become the main data set. Data from the clinic and saliva analyses will be added to said file upon completion and a second member of the research team will go through the imputed information to check for any errors. Regular back-ups will be made in the study folder on the protected research server/computers to prevent loss of data. Verbally recorded informed consent will be recorded in the electronic participant folder and signed paper forms will be stored at the clinic.

### Confidentiality {27}

The participant’s name and their unique code will be recorded on a separate list that will be stored in a separate location from the master list at the clinic. Once the study is completed, the list that contains the participant’s name and which unique code they received will be combined with the master list, along with clinic data including probing depth and anthropometric measurements. In order to maintain participant confidentiality, only the participant’s unique code and their corresponding data will be exported from the clinic to conduct the analyses. Saliva samples will be labeled with the participant’s unique code and the researcher conducting the analysis will not know whom they belong to. Dietary questionnaires will also be completed using the unique code.

### Plans for collection, laboratory evaluation, and storage of biological specimens for genetic or molecular analysis in this trial/future use {33}

Saliva samples will be stored at Brock University and any remaining sample will be destroyed after 10 years.

## Statistical methods

### Statistical methods for primary and secondary outcomes {20a}

Data will be entered into excel by a member of the research team. Another member will double-check the numbers and values to ensure the accuracy of data entry. Statistical analyses will be performed using IBM SPSS 26 statistical software and significance will be determined when *P* < 0.05. Mean and standard deviations will be reported for outcomes. Analysis of baseline participant demographics will be calculated to ensure consistency between the groups. The Kolmogorov-Smirnov test will be used to test the normality of the data. Levene’s test will be used to assess the equality of variances. Probing depths outcomes will be analyzed using an independent sample *t* test for the mean change in the number of PD ≥ 4 mm. If the data is not normally distributed, a Mann-Whitney test will be used. BOP is a categorical variable and chi-square analyses will be performed to measure the associations between the presence of bleeding and the treatment group.

The concentrations of the four salivary biomarkers and the quantitative values of the four periodontal pathogens at all three sample collection times will be log transformed to normalize their distribution. Two-way repeated measures analysis of variance (ANOVA) using treatment × time will be used to analyze each biomarker and pathogen individually. A repeated-measures ANOVA with Tukey’s post hoc test will be used to determine changes in energy and macronutrient intakes over the 3 visits in the intervention and control groups.

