#### Periodontal examination

All periodontal examinations will be completed by Registered Dental Hygienists with 15 years or more of experience using a periodontal probe. Multiple hygienists will participate in this study and to ensure consistency among measurements, they will be calibrated to apply 25 N of pressure by using an electronic scale [27]. Six PD sites will be measured on all teeth and implants (mesiobuccal, buccal, distobuccal, mesiolingual, lingual, and distolingual) as previously described [27]. The total number of sites with probing depths ≥ 4 mm will be measured. BOP will be measured by visual inspection and expressed as either absent or present at each of the sites.

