#### Sample size for full trial

The number of sites with probing depths ≥ 4 mm was used to determine sample size, as ST has been shown to reduce BOP to minimal levels to the point where an adjunct could not increase the effectiveness [3]. Previous literature has reported the mean change in number of sites with probing depths ≥ 4 mm from baseline to an average follow-up of 10.86 weeks is a mean of 81 with a standard deviation of 21 [3]. It has been shown that a high fiber diet can result in a 4% decrease in average PD though these participants were not diagnosed with periodontal disease and were not undergoing treatment with ST [24]. We believe it is reasonable to estimate that participants who are suffering from this disease and have deeper probing depths will experience a greater reduction in PD ≥ 4 mm in combination with ST (10%), as baseline PD is positively associated with follow-up PD [3]. Thus, the estimated mean change in the number of sites with probing depths of ≥ 4 mm is 91. Using a power of 80% and an alpha of 0.05, the total number of participants needed per group is 71. A 20% drop-out rate is estimated; the sample size for the full trial is 85 per group or a total of 170 participants. The sample size needed for the full trial was estimated using a statistical software (G*Power 3.1).

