### Methods for additional analyses (e.g., subgroup analyses) {20b}

The study will also determine if there is a difference in the effect of inulin on the primary outcomes in terms of BMI. Subgroup analyses for the number of sites with PD ≥ 4 mm will be performed using two categories for BMI: normal BMI (< 25 kg/m^2^) or overweight/obese (≥ 25 kg/m^2^). This analysis will be conducted using an independent sample *t* test. Chi-square analyses will be performed for BOP.

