This study will contribute to a better understanding of the role of inulin, a type of prebiotic, and periodontal disease. To our knowledge, no direct intervention with prebiotic supplementation to support the effectiveness of ST for periodontal disease has been conducted. Though, there is evidence that a higher intake of dietary fiber supports periodontal health. Dietary fiber may act as a mechanical force on the dental surfaces to aid in the shedding of the periodontal-associated pathogens in the microbial biofilm [35]. We will determine if a supplement can still be effective for periodontal health, given the lack of mechanical force needed for digestion of the inulin supplement to be provided.

This unique study design allows us to measure the response of inulin prior to and after sanative therapy. We can determine if inulin can improve periodontal biomarkers alone and if inulin can be considered an adjunct to ST. Salivary biomarkers are likely to change prior to improvements in clinical outcomes, which is why we are measuring salivary biomarkers and periodontal pathogens but not clinical outcomes at Visit II. The first 4 weeks of the intervention prior to ST will be used to assess the response of inulin alone; we predict that inulin supplementation may be able to decrease salivary markers of inflammation and periodontal-associated pathogens. The remaining 10 weeks will compare ST to ST and inulin supplementation. It is hypothesized that the inulin group will have a greater reduction in the number of sites with PD ≥ 4 mm and for the percentage of sites with BOP. Further, the subgroup analyses are anticipated to show that the response is greater in participants who are overweight/obese.

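### The chi-square planned for the primary BOP outcome names no unit of analysis: at site level its variance is wrong, and coded as any bleeding per participant it does not address the percentage of sites

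*Protocol article*

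**What the plan says.** The primary outcomes in Outcomes {12} are a reduction in the number of sites with probing depth (PD) of 4 mm or more and a reduction in the presence of BOP. Objectives {7} uses the same terms.

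Under Periodontal examination, "Six PD sites will be measured on all teeth and implants", and "BOP will be measured by visual inspection and expressed as either absent or present at each of the sites". Each participant therefore supplies many binary values. Trial design {8} randomises participants.

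The Discussion expects the inulin group to show a "greater reduction in the number of sites with PD ≥ 4 mm and for the percentage of sites with BOP".

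For analysis, section {20a} states: "BOP is a categorical variable and chi-square analyses will be performed to measure the associations between the presence of bleeding and the treatment group". Section {20b} repeats the method for the BMI subgroups: "Chi-square analyses will be performed for BOP". The paragraph of {20a} that names this test handles PD differently, as a mean change per participant compared by t test.

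The sample size rests on PD alone, because "ST has been shown to reduce BOP to minimal levels to the point where an adjunct could not increase the effectiveness".

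**The concern.** A Pearson chi-square assumes independent observations. Sites in one mouth share a host, oral hygiene and an examiner, so they are not independent. The article fixes this test for a primary outcome without saying whether it counts sites or participants, and the two natural readings fail in different ways.

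- **Sites as the unit.** The standard error is too small, and a chance difference could be reported as a positive primary result.
- **Participants as the unit, any bleeding or none.** The size of the test is right. But a fall from many bleeding sites to a few counts as no change, so the stated hypothesis on the percentage of sites is not examined.

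On neither reading does the baseline value enter, although the outcome is worded as a reduction. The BMI subgroup analysis inherits the problem.

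**Working it through.** **Inputs from the article.** Six sites per tooth or implant; alpha 0.05; 71 evaluable participants per group; for PD, a control change that "is a mean of 81 with a standard deviation of 21", against 91 with inulin.

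**Assumptions, because the article gives no figure.**
- Sites per mouth: 150 (25 teeth × 6), with 81 as a low value. The mean PD change is itself 81 sites, so an average mouth cannot have had fewer.
- Within-mouth correlation (ICC): 0.01 to 0.20.
- Sites bleeding after sanative therapy (ST): 3% to 30%.
- Effect: a 20% relative reduction in site bleeding.
- Two-sided tests and equal numbers of sites per mouth.

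**Step 1: the plan's own figure.** A two-sided t test for a difference of 10 with SD 21 at 80% power needs 70.2 per group, rounded up to 71. This reproduces: "Using a power of 80% and an alpha of 0.05, the total number of participants needed per group is 71". No power figure is given for BOP.

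**Step 2: sites as the unit.** Design effect DE = 1 + (m − 1) × ICC. Real size of a nominal 5% test = 2[1 − Φ(1.96/√DE)].

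| Sites m | ICC | DE | 1.96/√DE | Real type I error |
|---|---|---|---|---|
| 81 | 0.01 | 1.80 | 1.461 | 0.14 |
| 81 | 0.05 | 5.00 | 0.877 | 0.38 |
| 150 | 0.01 | 2.49 | 1.242 | 0.21 |
| 150 | 0.02 | 3.98 | 0.982 | 0.33 |
| 150 | 0.05 | 8.45 | 0.674 | 0.50 |
| 150 | 0.10 | 15.9 | 0.492 | 0.62 |
| 150 | 0.20 | 30.8 | 0.353 | 0.72 |

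At ICC 0.20, 71 × 150 = 10,650 sites per arm carry the information of 10,650/30.8 = 346 independent ones. A beta-binomial simulation (71 per arm, 150 sites, 4,000 runs per setting) gave 0.33–0.34, 0.49–0.50, 0.62–0.63 and 0.72–0.73 at ICC 0.02, 0.05, 0.10 and 0.20. In the same runs a t test on each participant's percentage of bleeding sites rejected in 0.046 to 0.055.

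**Step 3: participants as the unit, any bleeding or none.** P(at least one bleeding site of 150) comes from the beta-binomial. Chi-square power uses the usual normal approximation for two proportions. Power on the percentage scale is Φ(difference/SE − 1.96), where SE² = [p₁(1 − p₁) + p₂(1 − p₂)] × DE/(150 × 71).

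Example with 20% against 16% of sites bleeding and ICC 0.20:
- Any bleeding: 95.6% against 91.6% of participants, power 0.16.
- Percentage scale: SE² = (0.1600 + 0.1344) × 30.8/10,650 = 0.000851, so SE = 0.0292. Then 0.04/0.0292 − 1.96 = −0.59, and power is 0.28.

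| Sites bleeding, control | ICC | Participants with any bleeding, control / inulin | Power, any-bleeding chi-square | Power, percentage of sites (unadjusted) |
|---|---|---|---|---|
| 30% | 0.05 | 100% / 100% | 0.03 | 0.93 |
| 30% | 0.20 | 99.1% / 97.7% | 0.10 | 0.43 |
| 20% | 0.05 | 100% / 99.9% | 0.04 | 0.74 |
| 20% | 0.20 | 95.6% / 91.6% | 0.16 | 0.28 |
| 10% | 0.05 | 98.6% / 96.7% | 0.11 | 0.42 |
| 10% | 0.20 | 78.4% / 70.6% | 0.19 | 0.15 |
| 5% | 0.10 | 73.5% / 65.4% | 0.18 | 0.14 |
| 5% | 0.20 | 53.3% / 45.6% | 0.15 | 0.09 |
| 3% | 0.10 | 54.8% / 47.0% | 0.15 | 0.10 |
| 3% | 0.20 | 36.6% / 30.5% | 0.12 | 0.07 |

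**The case against.** Several points on the other side stand and limit the finding.

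- **No unit is stated.** A reader might infer that the trial will pool sites as independent. The article does not say so, and a condensed article may leave the variable definition to a fuller plan. The inflated type I error is therefore conditional. A participant-level classification other than any bleeding would also give a chi-square of correct size.
- **The any-bleeding table is not always degenerate.** A reader might infer that it is nearly uninformative in general. The article itself expects BOP to become minimal after ST. At 3% to 5% of sites bleeding with ICC 0.10 to 0.20, only 37% to 73% of control participants are positive. Any-bleeding power (0.12 to 0.18) then slightly exceeds the unadjusted percentage comparison (0.07 to 0.14). Much of the weakness there is the floor effect that the article acknowledges.
- **The hypothesis is not missed on every reading.** A site-level chi-square does compare pooled percentages of bleeding sites; its variance is wrong, not its target. The phrase about percentage of sites is also Discussion wording, whereas the objective and outcome sections speak of presence of BOP, as {20a} does.
- **Leaving out baseline is not an invalidity.** Under randomisation an unadjusted follow-up comparison is valid. The loss is mainly of precision.
- **The sizes rest on assumed inputs.** Neither the sites per mouth nor the correlation is in the article.

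These points do not rescue the plan as written. Recording is per site, no participant-level BOP variable is defined anywhere, and a specific test has been named for a primary outcome. This is a mismatch in what is stated, not merely detail left for later.

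**Conclusion.** The finding holds in conditional form. As stated, the chi-square does not give a dependable test of the BOP hypothesis under either natural reading.

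At site level the real type I error is about 14% (81 sites, ICC 0.01) to 72% (150 sites, ICC 0.20). It is inflated at every combination examined.

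Coded as any bleeding or none, the test is valid but does not address the percentage of sites. For a 20% relative reduction with 71 per arm its power stays below 20%. On the percentage scale, power is about 28% to over 90% when 20% or more of sites bleed. When bleeding is minimal and clustering strong, both approaches have low power, and changing the scale alone does not cure that.

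The existence of the site-level fault needs only a positive within-mouth correlation; its size depends on the assumed sites and ICC. Whether the trial would commit it cannot be settled from the article.

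**What to change.** In {20a} and {20b}, replace the chi-square for BOP with one of the following, and state the unit of analysis:

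- each participant's percentage of bleeding sites at Visit III, compared between groups by ANCOVA with the Visit I percentage as covariate, using robust or rank-based inference if percentages cluster near zero; or
- a logistic GEE or mixed model on sites, with participant as the cluster and baseline BOP as covariate.

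Then word the BOP outcome identically in Objectives {7}, Outcomes {12} and the Discussion, for example as the percentage of sites with BOP per participant.

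The cost is wording and slightly more analysis work. BOP is already collected at both visits, and the software already named can fit these models. The p-value may be less favourable than one from pooled sites.

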### Trial design {8}

A pilot study will be embedded within the randomized controlled trial with the first 48 participants. Once the pilot study is completed and the feasibility has been established, these participants will be included in the full trial. This is a single-center, randomized, double-blind, placebo-controlled study. The flowchart of the study is presented in Fig. 2. Participants will be randomly allocated in a 1:1 ratio into the intervention group (*N* = 85) or control group (*N* = 85).

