#### Dietary assessment

Dietary intakes will be measured using the Canadian version of the Automated Self-Administered 24-hour (ASA24®) Dietary Assessment Tool. The ASA24 will be completed online by participants and food intakes will be recalled over a 24-h period. ASA24 features two web-based applications, one that the participant will use to complete dietary recalls and one for the researcher to access nutrient analyses. Participants will be asked to complete 3 dietary assessments at each visit time point (two weekdays and one weekend day) to obtain an accurate representation. Participants will be given their username and password for the ASA24 respondent website so that they can complete the dietary assessments at home. The username will match their unique code administered on the intervention package. Participants will complete the first set of recalls before they begin the intervention. For Visits II and III, the research team will email or call the participant a week before their upcoming appointment and instruct them to log on to the ASA24 website and complete a set of food recalls before they return to the clinic for their next visit. Total energy intake, protein, fat, and carbohydrate intakes will be extrapolated from the assessments for the analysis. The means of each nutrient will be taken from the 3 recalls for each visit.

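### The diet outcomes are given a test of change over visits in the two groups, with no treatment factor or between-arm contrast named, so as written the plan does not estimate inulin's effect on intake

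*Protocol article*

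**What the plan says.** The Protocol article lists changes in energy, carbohydrate, fat and protein intake under Secondary outcome measures. Intake is measured at three visits by repeated 24-hour recalls: "The means of each nutrient will be taken from the 3 recalls for each visit" (Dietary assessment). The design is a parallel-group comparison: "Participants will be randomly allocated in a 1:1 ratio into the intervention group" (Trial design {8}).

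Section {20a} assigns a method to each family of outcomes:

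- **Probing depth:** an independent-sample t test (or Mann-Whitney) on the change in the number of sites.
- **Bleeding on probing:** a chi-square test of bleeding against treatment group.
- **Biomarkers and pathogens:** "Two-way repeated measures analysis of variance (ANOVA) using treatment × time will be used to analyze each biomarker and pathogen individually".
- **Diet:** "A repeated-measures ANOVA with Tukey’s post hoc test", which "will be used to determine changes in energy and macronutrient intakes over the 3 visits in the intervention and control groups".

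The common threshold is "significance will be determined when *P* < 0.05".

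**The concern.** In the first three families the comparison of arms is explicit. In the diet sentence it is absent: the stated aim is change across visits, and the arms appear only as the places where that change is looked for.

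Change over 14 weeks within one arm mixes any effect of inulin with whatever else moves reported intake, such as drift or the effect of repeating the recalls. Randomisation removes these only through the difference between arms. A significant change in one arm and a non-significant one in the other is not a test of that difference.

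Four listed outcomes are involved. The Background links fibre, fruit and vegetable intake to periodontal outcomes, so readers of the results will want to know whether the two arms' diets diverged. Separate tests of time in each arm cannot tell them.

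**Working it through.** **1. What the wording points to.** Three features of section {20a} favour a test of time within arms:

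- The stated purpose is change over the three visits.
- Tukey's procedure is for three or more means. There are three visits but only two arms.
- The adjacent sentence on biomarkers says that its ANOVA is two-way and names treatment × time. The diet sentence does neither.

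No other section supplies a between-arm test of intake.

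**2. The plan's own figure.** No figure is given for the diet analysis. The nearest anchor is the group size: "Using a power of 80% and an alpha of 0.05, the total number of participants needed per group is 71". The control change in sites "is a mean of 81 with a standard deviation of 21", and the inulin change is taken as 91, a difference of 10. The normal approximation, two-sided at 0.05, is

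n = 2 × (1.960 + 0.842)² × 21² / 10² = 69.2, so 70 per group.

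The t-based solution is 70.2, rounded up to 71. The stated 71 reproduces, and it is used as the group size in step 4.

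**3. How often two within-arm tests disagree.** Suppose that both arms truly change by the same amount and each within-arm test has power p. The arms are independent, so

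P(exactly one significant) = 2p(1 − p).

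- p = 0.30: 2 × 0.30 × 0.70 = 42%
- p = 0.50: 2 × 0.50 × 0.50 = 50%
- p = 0.80: 2 × 0.80 × 0.20 = 32%

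A between-arm test at the 0.05 level would be falsely significant in about 5%. The values of p are assumptions, because the documents give no standard deviation, correlation or expected drift for intake.

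**4. Check by simulation.** 4,000 trials per row, 71 per arm, three visits, normal data. Assumed: within-person correlation 0.5 and the same linear drift in both arms, given as the total change from Visit I to Visit III in SDs of intake at one visit. There is no true difference between arms.

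| Common drift (SD) | One arm significant (inulin) | Exactly one arm significant | Treatment × time significant |
|---|---|---|---|
| 0 | 5.3% | 10.7% | 5.4% |
| 0.1 | 11.2% | 20.1% | 5.3% |
| 0.2 | 29.5% | 41.6% | 4.7% |
| 0.25 | 46.0% | 50.3% | 5.1% |
| 0.3 | 61.0% | 47.1% | 4.4% |
| 0.4 | 85.5% | 25.1% | 5.7% |

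The third column agrees with 2p(1 − p) at the p in the second column; for example, 2 × 0.295 × 0.705 = 41.6%. Disagreement ranges from 10.7% to 50.3% over the drifts tried, while the treatment × time test stays between 4.4% and 5.7%.

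**The case against.** The strongest objection is that the sentence does not say that the ANOVA is run separately in each group. It names both groups in one analysis, and a repeated-measures ANOVA with group as a between-subject factor would fit those words. Tukey's test does not settle the matter, since it could be applied to the six group-by-visit means (2 × 3). This stands. A reader might infer that the plan cannot show any effect of inulin on diet, or that the randomised comparison has been thrown away; the text does not support that much. It does support saying that no arm comparison is specified, in contrast to the neighbouring sentence.

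Model terms are often left to an analysis plan, and one may exist. But here the protocol does not leave the method open. It states a method and its purpose, and that purpose is change over visits.

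The disagreement rates apply only if someone reads the two within-arm results against each other. The protocol does not announce that inference, so the rates show what would follow from it and are not an error rate of the plan.

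A reader might also suspect regression to the mean. The eligibility criteria do not select on energy or macronutrient intake, so nothing in the documents would produce a systematic shift of that kind.

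Finally, diet is not named in the stated objectives or hypotheses, and no section uses intake to explain or adjust the periodontal result. That limits the weight of the point, but the four intakes remain listed secondary outcomes.

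**Conclusion.** The point holds in a limited form. For four listed secondary outcomes, section {20a} specifies a test of change over visits and no comparison of arms. On its natural reading this does not estimate the effect of inulin on diet. If a model with group as a factor was intended, the text does not say so, and the same correction is needed.

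The size is conditional. Comparing within-arm results informally would suggest a difference that does not exist in 32% to 50% of trials at within-arm power between 30% and 80%, and in 10.7% even with no drift at all. A between-arm test gives about 5%. These figures rest on equal true change in both arms and on assumed power, or on assumed drift and correlation.

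The primary analyses of probing depth and bleeding are untouched, because both already compare arms. The change is worth making because it is specific and nearly free; it does not threaten the main conclusion.

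**What to change.** Replace the diet sentence in section {20a} with a between-arm analysis of each of the four intakes. Two forms would do:

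- **Minimum:** the two-way repeated-measures ANOVA with treatment × time that is already planned for the biomarkers and pathogens.
- **Preferred:** Visit II and Visit III intakes compared between arms, adjusted for baseline intake. This is a different model from the biomarker ANOVA, so the text should say which of the two is used.

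In either case, report the treatment difference with its 95% CI at Visit II and at Visit III, and keep within-arm changes as description without using them to infer an effect of inulin.

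The cost is one sentence in the analysis section. No new data, visits or participants are needed.
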